### 8.3 HANDLING OF WITHDRAWALS

Parents that wish to withdraw their child's participation from the trial may do so at any stage of the study, without giving a reason and without any change to any aspect of treatment or relationship with the treating medical team. Parents of any child who is withdrawn from the study after randomisation and before or after the intervention is administered will be asked to allow collection of de-identified data. In our experience, based on currently ongoing and past prospective studies, participants withdrawing after providing consent is extremely uncommon.

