### 8.4 REPLACEMENTS

Withdrawn participants will be replaced in the study. In Australia, New Zealand and other participating centres, a good neuro-developmental follow up exists as a standard practice where children born this young, are routinely followed up for 5 years and their developmental assessment is performed. To facilitate and ensure good long term follow up, existing measures which are standard practices includes providing appointment letters by post, reminding and confirming with families by phone and/or text message when follow up appointment is close to date.

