## 9. STATISTICAL METHODS

### 9.1 SAMPLE SIZE ESTIMATION & JUSTIFICATION

A 50% reduction in mean burden of hypoxia and hyperoxia in active treatment relative to control would be considered worthwhile. This corresponds to a reduction of 0.3 in the mean of log-transformed burden. In the Safe BoosC II study (BoosC results) a 58% reduction was achieved. Assuming a standard deviation of 0.5 in log-transformed burden (Ref – BoosC protocol), this would require 45 babies per group to achieve 80% power at 5% two-sided alpha. To account for the clustering effect of twins being allocated to the same treatment, we assume that 30% of babies are twins (giving an average cluster size of 1.3, and a within-twin correlation of 0.1 in the outcome. This gives a design effect of 1.03 by which the sample size is adjusted, leading to a sample size of 47 per group, 94 babies in total. We aim to recruit 100 babies to account for some loss to follow-up or missing data.

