## **SAMPLE SIZE**

Based on the results of the Safe-BoosC-II study, a 50% reduction in mean burden of hypoxia and hyperoxia in active treatment relative to control would be considered worthwhile. This corresponds to a reduction of 0.3 in the mean of log-transformed burden of cerebral hypoxia and/or hyperoxia. In the Safe BoosC-II study, a 58% reduction was achieved. Assuming a standard deviation of 0.5 in log-transformed burden, this would require 45 babies per group to achieve 80% power at 5% two-sided alpha. To account for the clustering effect of twins being allocated to the same treatment, we assume that 30% of babies are twins-based on regional incidence of twin births (giving an average cluster size of 1.3, and a within-twin correlation of 0.1 in the outcome. This gives a design effect of 1.03 by which the sample size is adjusted, leading to a sample size of 47 per group, 94 babies in total. We aim to recruit 100 babies to account for some loss to follow-up or missing data. For consented participants, if the NIRS monitoring was discontinued earlier than 5 days after birth, data collected until discontinuation of monitoring will be used for analysis of the primary outcome.

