### *Analysis of the outcomes*

Participant demographic and clinical characteristics and study outcomes will be presented using standard descriptive statistics: frequencies and percentages for categorical variables, mean, standard deviation and range or median, quartiles and range for continuous variables. All efficacy analyses will be performed according to randomized treatment. We will use a suitable transformation to ensure normality for the primary outcome, the burden of cerebral hypoxia and hyperoxia and use generalized estimating equation (GEE) or a similar method for comparison between groups. Sub-group analysis for stratification variables will be performed. For reporting the burden of cerebral hypoxia and hyperoxia, we will include deviations in cerebral oxygenation more than a minute. This pragmatic approach will ensure we achieve a balance between responding to an alarm from poor sensor contact with the participant and identifying true real-time changes in cerebral oxygenation. To allow comparison of the primary outcomes with other studies, we will also report the burden of cerebral hypoxia and hyperoxia more than 10 minutes. Other study outcomes will be compared using similar methods, using GEE methods with normal or binary outcome distribution and correlation between outcomes in twins. Adjusted models will explore predictors out outcomes. No corrections for multiple hypotheses will be performed. Adjusted models will be used to explore predictors of outcomes. Variables that differed significantly between the two groups, and could plausibly contributory to the outcome, will be considered for adjustment. A fixed adjustment for gestational age category will be included as an a priori specified variable. For this trial, no imputation of missing data will be performed and sensitivity analysis will only be performed separately for the burden of cerebral hypoxia and cerebral hyperoxia. In future, sensitivity analysis may be performed for variables such as specific gestational age or treatment received.

Withdrawn participants will be replaced in the study with new randomisation (per protocol). To facilitate and ensure long term follow up, existing measures which are standard practices includes providing appointment letters by post, reminding and confirming with families by phone and/or text message when follow up appointment is close to date.

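### Withdrawn infants are replaced by newly randomised ones, and the plan does not say consistently whether a replaced infant stays in the analysis

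*Combined protocol and SAP*

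**What the plan says.** **Replacement.** Protocol 8.4: "Withdrawn participants will be replaced in the study". The SAP (Analysis of the outcomes) adds the mechanism: "Withdrawn participants will be replaced in the study with new randomisation (per protocol". The new infant therefore takes the next allocation on the list, not the withdrawn infant's arm.

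**Withdrawal.** Protocol 8.3 leaves the decision to the family: "Parents that wish to withdraw their child's participation from the trial may do so at any stage of the study, without giving a reason". Parents of a withdrawn infant "will be asked to allow collection of de-identified data", so use of the data depends on permission. The same section says "participants withdrawing after providing consent is extremely uncommon" and gives no rate.

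**Analysis set.** The opening sentence of the SAP's Statistical analysis section calls the analysis per-protocol. Protocol 9.3 and the SAP's Analysis of the outcomes say efficacy is analysed by randomised treatment. The SAP plans no imputation, and its only sensitivity analysis separates hypoxia from hyperoxia.

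**Limits on data use.** Protocol 7.4 bars use of data without consent. The subsection that follows it removes data for some infants who die or become critically ill before their parents can be approached.

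**Sample size.** Protocol 9.1 derives 94 and then says "We aim to recruit 100 babies to account for some loss to follow-up or missing data". The SAP has the same sentence.

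**The concern.** Replaced ordinarily means substituted. Read with the per-protocol statement, the rule lets an analyst drop a randomised infant who has usable, permitted data and count the newcomer instead. Read with the randomised-treatment statement, the same documents keep that infant. Two analysts could both follow the plan and report different primary results.

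Withdrawal happens after allocation. Protocol 6.4 says clinical staff know the arm, and readings are visible only in the intervention arm. For infants enrolled under the consent waiver, protocol 7.1 has a research or clinical team member seek consent to continue during the first 5 days. If families of infants with a difficult course withdrew more often in one arm, dropping those infants would make that arm look better. No planned analysis would show it.

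**Working it through.** **1. The plan's sample size.** Inputs from protocol 9.1 and the SAP: difference 0.3 in log burden (log10 of 0.5 is -0.301), SD 0.5, 80% power, two-sided 5%.
- Two-sample t-test, effect size 0.3/0.5 = 0.6: 44.59, so 45 per group, as stated.
- Design effect 1 + (1.3 - 1) × 0.1 = 1.03. Then 45 × 1.03 = 46.35, so 47 per group and 94 in total, as stated.
- The margin is (100 - 94)/100 = 6%.

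**2. Is replacement needed for power?** Randomise 100, replace no one, and take effective n per group = analysed/(2 × 1.03).

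| Overall loss | Analysed | Power (t-test) | Randomised if replaced up to 100, 100/(1 - loss) |
|---|---|---|---|
| 0% | 100 | 83.3% | 100 |
| 5% | 95 | 81.3% | 105 |
| 6% | 94 | 80.9% | 106 |
| 10% | 90 | 79.2% | 111 |
| 20% | 80 | 74.2% | 125 |

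Up to 6% loss, the existing margin keeps power at about 81%.

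**3. Does replacement itself cause bias?** This was simulated with no true effect, 8,000 trials per setting and independent infants. Assumptions: withdrawals occur only in the intervention arm, withdrawal propensity has a given correlation with log burden, and recruitment continues until 100 infants have not withdrawn.

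| Withdrawal in that arm, correlation | Withdrawn kept: mean difference, type I error | Withdrawn excluded: mean difference, type I error |
|---|---|---|
| 10%, 0 | 0.002, 5.2% | 0.002, 5.3% |
| 10%, 0.6 | -0.001, 5.2% | -0.059, 9.1% |
| 20%, 0.6 | 0.001, 5.4% | -0.103, 18.3% |

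Replacement is identical in both columns of results, so the bias comes from exclusion. The kept column assumes that withdrawn infants have a usable burden value.

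**4. Range for exclusion.** Shift = -correlation × 0.5 × φ(z)/(1 - w), where w is the share of one arm withdrawn and z the normal quantile at 1 - w. SE = 0.5 × √(2 × 1.03/50) = 0.1015. Type I error = P(|Z + shift/SE| > 1.96).
- w = 5%, correlation 0.3: shift -0.016, type I error 5.3%.
- w = 10%, correlation 0.6: shift -0.0585 (burden ratio 0.87), type I error 8.9%.
- w = 20%, correlation 0.6: shift -0.105 (burden ratio 0.785), type I error 17.9%.

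**5. In counts of infants.** Suppose k infants from the highest quarter of burden (mean 1.271 SD above average) leave one arm of 50 and average infants take their places in that arm. Shift = k × 0.5 × 1.271/50 and SE = 0.5 × √(2/50) = 0.10.
- k = 1: shift 0.013, type I error about 5.2%.
- k = 3: shift 0.038, type I error about 6.7%.
- k = 5: shift 0.064, which is 21% of the 0.3 target; type I error about 9.7%.

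With k = 5 excluded and nobody added, the shift is 5 × 0.6355/45 = 0.071. Replacement slightly dilutes the bias.

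**The case against.** The best defence is that replacement by a new randomisation may only mean recruiting one more infant, with the withdrawn infant still analysed as randomised. Step 3 supports this: on that reading the comparison is unbiased and N rises. The SAP's per-protocol sentence might also mean only that the protocol will be followed. Both readings are possible, but the documents do not settle on either, and per-protocol is the usual name for a restricted analysis set. The gap stands.

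A reader might infer four stronger points that the documents do not support.
- **That an infant cannot be both replaced and analysed, so the rule breaks randomisation by itself.** It can be both. Deleting the rule would not remove the harm unless the analysis set is also fixed.
- **That withdrawn infants' data are certain to be kept, in contradiction of replacement.** Protocol 8.3 only asks permission.
- **That the SAP's sample size section contradicts replacement.** Its statement that "data collected until discontinuation of monitoring will be used for analysis of the primary outcome" concerns consented infants whose monitoring stopped early, which is a different event from leaving the trial.
- **That unblinded staff decide who withdraws.** Parents decide. Whether they know the arm is not stated, and influence by staff is inference.

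The objection that withdrawal will be rare also carries weight. But the protocol's remark covers withdrawal after consent has been given. It does not cover families enrolled under the waiver who decline, and no section says whether they count as withdrawn and are replaced.

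The SAP already commits to CONSORT reporting, so a hidden loss should not be presumed.

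**Conclusion.** The point holds as an unresolved analysis set. Replacement is prescribed twice, the two descriptions of the analysis conflict on their ordinary meaning, and no sentence says whether a replaced infant with permitted data is analysed. Bias needs three things together: replaced infants are dropped, withdrawal is related to burden, and withdrawal differs by arm. Under the assumed one-sided withdrawal of 5% to 20% and correlation of 0.3 to 0.6, type I error is 5.3% to 17.9%. With one such infant it is about 5.2%, and with no relation to burden it stays near 5%. The documents give neither a withdrawal rate nor a correlation, so these figures show a range and are not a forecast. If withdrawal is as uncommon as protocol 8.3 says, the effect is negligible. This is a cheap improvement and not evidence that the trial's result would be wrong.

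**What to change.** 1. In protocol 8.4 and the SAP's Analysis of the outcomes, say that replacement removes no one from the analysis, and that any extra infants add to the randomised total and stand in for nobody.
2. In the SAP's Statistical analysis section, replace the per-protocol wording. Every randomised infant whose data may be used, subject to protocol 7.4, the subsection after it on parents who cannot be approached, and 8.3, is analysed in the allocated arm with all data up to withdrawal.
3. State whether 100 counts randomised or analysed infants. If it counts analysed infants, the number randomised will be larger (105 at 5% loss, 111 at 10%).
4. Say whether a family enrolled under the waiver who declines counts as withdrawn. Report withdrawals and non-consent by arm and timing in the CONSORT flow.

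The cost is wording. The number with complete 5-day recordings may end slightly below 100. The existing margin covers that up to 6% loss in all, including data removed for lack of consent; at 10%, power is 79.2%. Where permission is refused the infant is still lost, and the fix cannot recover it. Reporting by arm lets a reader judge whether that matters.
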